## Abstract

**Background:**

Obstetric fistula is a serious medical condition which affects women in low income countries. Despite the progress of research on fistula, there is little data on long term follow-up after surgical repair. The objective of this study is to analyse the factors associated with the recurrence of fistula and the outcomes of pregnancy following fistula repair in Guinea.

**Methods:**

A descriptive longitudinal study design will be used. The study will include women who underwent fistula repair between 2012 and 2015 at 3 fistula repair sites supported by the Fistula Care Project in Guinea (Kissidougou Prefectoral Hospital, Labé Regional Hospital and Jean Paul II Hospital of Conakry).

Participants giving an informed consent after a home visit by the Fistula Counsellors will be interviewed for enrolment at least 3 months after hospital discharge The study enrolment period is January 1, 2012 − June 30, 2015. Participants will be followed-up until June 30, 2016 for a maximum follow up period of 48 months. The sample size is estimated at 364 women.

The cumulative incidence rates of fistula recurrence and pregnancy post-repair will be calculated using Kaplan-Meier methods and the risk factor analyses will be performed using adjusted Cox regression. The outcomes of pregnancy will be analysed using proportions, the Pearson’s Chi Square (*χ*2) and a logistic regression with associations reported as risk ratios with 95 % confidence intervals. All analyses will be done using STATA version 13 (STATA Corporation, College Station, TX, USA) with a level of significance set at *P* < 0.05.

**Discussion:**

This study will contribute to improving the prevention and management of obstetric fistula within the community and support advocacy efforts for the social reintegration of fistula patients into their communities. It will also guide policy makers and strategic planning for fistula programs.

**Trial registration:**

ClinicalTrials.gov Identifier: NCT02686957. Registered 12 February 2016 (Retrospectively registered).

## Background

Obstetric fistula (OF) is a serious medical condition in which a perforation develops between vagina, bladder and/or rectum, most commonly after prolonged labour when the head of the unborn child compresses the birth canal and leads to tissue necrosis [1, 2]. A recent study in 5 countries showed that women suffering from OF are generally married young, have little formal education and for most of them the fistula occurred after the first pregnancy, at a median age of 20 years [3]. The condition hardly exists in the developed world, but remains prevalent in sub-Saharan Africa, especially in countries where access to quality emergency obstetric care is low [4, 5]. Guinea for instance has a high maternal mortality ratio (724 per 100 000 live births) and a prevalence of OF among women of reproductive age estimated to be 0.6 %, which represents a total number of 15 − 18 thousands women living with an OF [6].

Thanks to the international mobilization against fistula in recent years, the holistic care of OF (prevention, treatment and reintegration) in many sub-Saharan African countries has improved [7, 8]. As a result, immediate post-operative closure rates of OF have increased [9–12]. In addition, the number of repaired women has increased worldwide with more than 30,000 fistula repairs supported by the Fistula Care Project in 15 countries since 2005 [13] and more than 57,000 repairs funded by the UNFPA over the past decade [14]. Furthermore, new evidence has shown that women’s hospital stay can be shorten and costs lowered, allowing more women to be treated [15]. In Guinea, about 3,000 fistulas were repaired between 2007 and 2013 by the Fistula Care Project (a USAID-funded project managed by EngenderHealth) [13, 16].

Despite these improvements, gaps still exist, especially in the long term follow-up of women after successful fistula repair [17]. In fact, data currently available show that delivery leading to fistula usually ends up with a stillbirth [10–12] and that women are relatively young at the time their fistula is repaired [3]. Therefore, when successfully repaired, women return to their community with the desire to resume social and sexual life, and have children [18–20]. However, this return to sexuality exposes repaired woman to pregnancy and childbirth, which increases the risk of recurrence of a previously repaired fistula or the formation of a second, new fistula [18, 19]. Fear of recurrence of fistula is a constant worry for women successfully repaired of OF [21–23] and, given the cost of fistula care and the lower success of repairing [24], these women might need more attention to prevent recurrence of fistula and adverse pregnancy outcomes.

There is no precise estimate of the recurrence of fistula or pregnancy after OF repair. In Ethiopia, Nielsen et al [18] observed 2.63 % re-occurrence of fistula among 38 women in a 21 months’ post-repair median follow up and Browning and Menber [19] recorded 4.26 % in 141 women successfully repaired after 6 months’ follow-up. In Malawi, Wilson et al [20] reported 3.85 % of re-occurrence in 26 women after 9 − 24 months’ follow-up post-repair.

The same authors found a proportion of pregnancies of respectively 13.16 % [18] and 4.26 % [19] in Ethiopia and 23.10 % in Malawi [20]. Delivery outcomes were poor with only 1 live birth reported in both Ethiopia and Malawi [18, 20]. Heavy work, sexual intercourse, and delivery have been reported to be associated with the recurrence of fistula [25–28]. Because sexuality and desire of children are part of women’s life after successful OF repair [18, 19, 21, 29] and recurrence of fistula and stillbirth are very common complications of delivery post OF repair [18, 20], there is a need for more well powered long term follow-up studies that could fill the existing gap of knowledge. The need to collect long-term follow-up data about fistula recurrence, subsequent pregnancies and their outcomes has already been identified among current research priorities on fistula [17]. Since, there has been no major comprehensive and well powered study initiated in a sub-Saharan African country involving women after OF repair, and for the status of the fistula at discharge is not always specified in the existing studies, we initiated this study with the following objectives:Analyse the incidence rate and risk factors of fistula recurrence up to 48 months follow up.Analyse the incidence rate and factors associated with pregnancy and pregnancy outcomes (maternal and perinatal) up to 48 months’ follow-up;

The endpoints will be recurrence of fistula, pregnancy, abortion or miscarriage, maternal, perinatal and child death at any time from hospital discharge.

## Methods

### Study design

This is a longitudinal follow-up study over a period of 4 years conducted among women underwent fistula repair at 3 sites supported by Engenderhealth in Guinea. A cohort will be constituted. Participants who have been repaired at OF treatment sites before the study has started will be included retrospectively and then followed up prospectively (Fig. 1).

**Fig. 1 Fig1:**
[figure not shown]
Study flow chart

The primary outcome is the incidence rate of the recurrence of fistula. For the purpose of this study, recurrence of fistula includes the breakdown of a repaired fistula or the occurrence of a new fistula in study participants. At the study sites, the closure of fistula was determined at hospital discharge by a pelvic exam using a dye test. During follow-up visits, women will first be asked about current medical status using the question “does the woman have continuous and uncontrolled leakage of urine?”. If the answer is “YES” then women will be scheduled for a pelvic exam with a dye test for confirmation, at the nearest health facility (health centre or health post). This question is always used at EngenderHealth supported sites to assess women at reception, before further pelvic exam. In addition, the presence of “continuous and uncontrolled leakage of urine” is commonly used as a screening question for fistula in circumstances in which a pelvic exam is not possible (e.g. Demographic and Helath Surveys, DHS); it differentiates between fistula and other forms of incontinence, which are unlikely to be continuous and uncontrolled. In some cases, it might not be feasible to perform the dye test if for instance the woman refuses to go to a health facility. This might lead to a misclassification which can bias the estimate towards a null. However, misclassification is unlikely, since women with continued urinary leakage are eager to report their experiences in order for the condition to be rectified.

The secondary outcomes include pregnancy and pregnancy and outcomes (miscarriage or abortion or term pregnancy). Pregnancy and pregnancy outcomes will be documented by a positive pregnancy test from discharge (done at recruitment or during follow-up visit or given at any time by a result from medical records such as antenatal (ANC) card) or by a self-reporting corroborated by 2 witnesses. Maternal status at delivery and mode of delivery (dead or alive; caesarean section or normal delivery; no complication or any complication) will be assessed by looking at the ANC & Delivery card or hospital records or self-reporting. Child outcome at delivery (stillbirth, neonatal death or alive) will be assessed by looking at the ANC & Delivery card or hospital records or self-reporting corroborated by 2 witnesses.

Our predictors of interest will include patient characteristics, fistula characteristics, context of repair and context of reintegration. Because women will be recruited and followed-up to record the occurrence of the study outcomes over a period of time, the longitudinal follow-up study design is the most suitable design.

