### Sample size calculation

For the estimation of the incidence rate of the recurrence of fistula, we used the 2-Sided Confidence Intervals for 1 Proportion Confidence Interval Formula [31]. Using the existing data [19] and considering a +/- 2 % margin of error and 95 % confidence interval, we estimate the sample size of the cohort to be 280. We anticipate 20 % loss to follow-up and 10 % refusal rate and accordingly increase the sample size to 364. The same formula provides an estimation of the sample size for the incidence rate of pregnancy [31]. If we estimate the rate of pregnancy to be around 20 % at 24 months’ follow-up among successfully repaired women [20], a sample size of 264 women produces a 2-sided 95 % confidence interval with 10 % precision. Therefore, the sample size of 364 women will be sufficient to describe the objective on pregnancy and its outcomes.

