### Data analysis

Categorical data and treatment outcomes will be summarized as frequencies (%) and compared using *χ*2 or Fisher’s exact tests as appropriate. Continuous data will be presented using median (interquartile range) and compared using the Wilcoxon rank-sum test. Follow-up will be calculated from the date of hospital discharge. The date of fistula recurrence or the estimated date of pregnancy will be selected as the date of events. Patients who do not experience recurrence of fistula or pregnancy will be censored at the last follow up visit. For patients who are reported dead (by the relatives), the date of death will be used to determine their follow-up time in the study. For patients who are lost to follow up (i.e. who move from their village without any address to joint them after inclusion) the date of the last visit will be used.

Socio-demographic and clinical differences between those women who remain in the study and those who are lost-to-follow-up will be estimated to check for any imbalances at inclusion.

The incidence of fistula recurrence and that of pregnancy will be estimated using the method of cumulative incidence. The cumulative incidence rate will be compared across risk factors using Kaplan-Meier methods. Exposure variables with a *P*-value <0.2 in the univariate analysis will be included in multivariate models. Exposure variables with a *P*-value <0.2 in the univariate analysis will be included in multivariate models. A risk factor analysis will be performed using adjusted Cox regression. Associations will be reported as adjusted hazard ratios with 95 % CIs. Analysis will be done using STATA version 12 (STATA Corporation, College Station, TX, USA) with a level of significance will be set at *P* < 0.05.

For the outcomes of pregnancy (miscarriage or abortion, mother and child status at delivery), Pearson’s Chi square (*χ*2) will be used to compare proportions of these outcomes between potential exposure variables (age group, previous repair (Yes/No), fistula status at hospital discharge, use of antenatal care, delivery by caesarean section, etc.). Logistic regression analysis and models will be used and associations will be reported as risk ratios with a level of significance set at *P* = 0.05 and a 95 % confidence intervals.

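### The ±2 % margin is for a fully observed proportion, not for the planned Kaplan-Meier cumulative incidence at the 48-month horizon, and the primary outcome is loosely called an incidence rate

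*Protocol article*

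**What the plan says.** All references are to the Protocol article.

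- **Objectives (end of Background):** "Analyse the incidence rate and risk factors of fistula recurrence up to 48 months follow up".
- **Study design:** "The primary outcome is the incidence rate of the recurrence of fistula". Recurrence covers both breakdown of the repair and a new fistula.
- **Sample size calculation:** the method is given as "For the estimation of the incidence rate of the recurrence of fistula, we used the 2-Sided Confidence Intervals for 1 Proportion Confidence Interval Formula". With a ±2 % "margin of error and 95 % confidence interval, we estimate the sample size of the cohort to be 280", raised to 364 for 20 % loss and 10 % refusal. No time point or censoring enters the calculation.
- **Source of the expected value:** the Sample size section cites an Ethiopian study, which the Background says "recorded 4.26 % in 141 women successfully repaired after 6 months’ follow-up".
- **Data analysis:** "The incidence of fistula recurrence and that of pregnancy will be estimated using the method of cumulative incidence". Follow-up starts at hospital discharge, and women without an event are censored at their last visit. The Abstract names Kaplan-Meier as the method.
- **Dates (Abstract; Participants' recruitment and follow-up):** repairs from 1 January 2012 to 30 June 2015, follow-up to 30 June 2016, stated maximum 48 months.

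**The concern.** The objective and the outcome definition use one term, the sample size uses a second quantity, and the analysis uses a third label. With unequal follow-up, a simple proportion and a Kaplan-Meier risk at a given time are not the same number and do not have the same precision.

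The simple-proportion margin assumes that every counted woman is observed for the whole period at risk. In this cohort women enter over 42 months and follow-up closes on one date, so late in follow-up the estimate rests on few women. The Background justifies the study by missing long-term data, and the Discussion describes the sample as well powered. A reader would therefore take ±2 % as the precision of the long-term recurrence figure.

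**Working it through.** **1. The plan's own figure.** For one proportion, n = z²p(1−p)/d². With z = 1.96, p = 0.0426 and d = 0.02, n = 3.8415 × 0.0426 × 0.9574 / 0.0004 = 392, not 280. The formula returns 280 at p = 3.0 %, a value the article does not state. At n = 280 and p = 4.26 % the half-width is 1.96 × √(0.0426 × 0.9574 / 280) = 2.4 points. The inflation reproduces: 280 × 1.30 = 364. The origin of 280 is a separate matter. What counts here is that this is a simple-proportion calculation.

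**2. Who can be observed how long.** From 30 June 2015 to 30 June 2016 is 12 months, and from 1 January 2012 to 30 June 2016 is 54. Assume repairs spread evenly over the 42 months and ignore the short gap from repair to discharge. The share able to reach month t is then (54 − t)/42: 71 % at 24 months, 43 % at 36, and 6/42 = 14 % at 48. If 20 % are lost at a uniform time within their own follow-up (assumption), the share at 48 months is 0.80 × 14.3 % = 11.4 %. That is about 42 of 364 women, before removing those with an event.

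**3. Expected Kaplan-Meier half-width.** The large-sample Greenwood form is

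1.96 × S(t) × √{ (1/n) ∫₀ᵗ h(u) / [S(u) G(u)] du },

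where h is the hazard, S the probability of no recurrence and G the share still observable from step 2. The hazard shapes are assumptions, because the article gives none:

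- A: all recurrences within 6 months, 4.26 % in total.
- B: 4.26 % by 6 months, then a quarter of that hazard.
- C: constant hazard giving 4.26 % at 24 months.
- D: constant hazard giving 4.26 % at 6 months.

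Half-widths at 48 months, in percentage points:

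| Shape | Risk at 48 months | Fully observed, n = 280 | Kaplan-Meier, n = 280, no loss | Kaplan-Meier, n = 280, 20 % loss | Kaplan-Meier, n = 364, 20 % loss |
|---|---|---|---|---|---|
| A | 4.3 % | 2.4 | 2.4 | 2.4 | 2.1 |
| C | 8.3 % | 3.2 | 4.6 | 5.0 | 4.3 |
| B | 11.3 % | 3.7 | 4.9 | 5.2 | 4.6 |
| D | 29.4 % | 5.3 | 7.7 | 8.3 | 7.3 |

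Simulating 3,000 cohorts per cell for the Kaplan-Meier columns agreed within 0.2 points.

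**4. Hand check for shape C, n = 280, no loss.** With a low constant hazard, the integral is proportional to 48 under full observation. With staggered entry it is proportional to 12 + 42 × ln(42/6) = 12 + 81.7 = 93.7. The variance rises by 93.7/48 = 1.95 and the width by √1.95 = 1.40. Then 3.2 × 1.40 = 4.5, against 4.6 in the table.

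**5. Earlier times.** For n = 364 with 20 % loss, the half-width is ±1.5 (C) and ±2.3 (B) at 12 months, and ±2.3 (C) and ±2.8 (B) at 24 months. The stated ±2 is thus roughly right early and wrong late.

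**The case against.** **Incidence rate is only a label.** This stands. A reader might infer that a rate per woman-year is the primary quantity and that the plan therefore mixes three different measures. The documents do not support that. No section gives a person-time denominator, the Abstract attaches the word rate to a Kaplan-Meier cumulative incidence, and the Sample size section calls 20 % pregnancy at 24 months a rate. The authors use rate for a cumulative proportion throughout.

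**Sizing a Kaplan-Meier estimate by a one-proportion formula plus a loss allowance is common, and a condensed article may leave the time point to the full protocol.** The first part is fair as a rough method and holds when most women reach the time point. At 48 months about one in seven can. The second part also stands: an unstated time point alone would not be a finding. The defect is that the article states a margin, a horizon and an estimator that do not fit together.

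**Precision is fine if recurrence is early.** True under shape A (±2.1 for 364 women). But the Background links recurrence to later pregnancy and childbirth, and the outcome includes new fistulas, so the plan itself expects later events.

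**The steepest shape is implausible.** Largely accepted. Shape D implies 1 − 0.9574^(21/6) = 14 % at 21 months, while the Background reports 2.63 % of 38 women (one woman) at a median of 21 months. Treating 21 months as fixed for all, 0 or 1 event in 38 at 14 % has a probability of about 2 %. The conclusion therefore rests on shapes B and C.

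**A 12-month primary time point might seem the obvious remedy.** The documents do not support it as such. It sits awkwardly with the 48-month aim, and not every woman can reach it: eligibility runs on the repair date, follow-up starts at the later discharge date, and censoring is at the last visit.

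**Conclusion.** The point holds as a mismatch between the stated precision and the planned estimate, together with a loose term for the primary outcome. If recurrence continues after 6 months at a moderate level (8 to 11 % risk at 48 months), the 48-month half-width is ±4.3 to ±5.2 points for 280 to 364 women, more than twice the stated ±2. Part of this is the higher risk at a longer horizon (±3.2 to ±3.7 for 280 women even if fully observed), and the rest is censoring. It would be wider under a higher constant hazard and about ±2 if all recurrences fell within 6 months.

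These figures assume evenly spread repairs, loss at a uniform time where 20 % loss is applied, and the hazard shapes listed. The planned estimator itself is suitable and the data remain usable. What needs correction is the wording of the outcome and the claimed precision.

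**What to change.** 1. In the objectives, Study design and Sample size sections, replace incidence rate by the Kaplan-Meier cumulative incidence of recurrence, measured from hospital discharge, at one time point. The investigators should name that time in advance so that it fits both the 48-month aim and the number of women still under observation.
2. In the Sample size section, restate the expected margin for that time point under explicit assumptions on risk, staggered follow-up and 20 % loss, preferably for more than one hazard shape.
3. State there that ±2 % is not the precision at 48 months.

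This changes wording and one calculation and needs no new data. The cost is a less favourable stated precision at the long-term horizon.

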### Participants’ recruitment and follow-up

All women who underwent successful repair of OF from January 1, 2012 to June 30, 2015 at the 3 study sites are eligible for inclusion in study. However, only women with a unique obstetric fistula that was closed at discharge, as measured by a dye test, who provide written informed consent, reside in Guinea and agree with follow-up visits will be included in the study (Fig. 1). Eligible participants who refuse informed consent, who got repair outside the study sites or whose medical records are incomplete will be excluded.

Individual medical records of all women who benefited fistula repair at the 3 sites in 2012–2015 will be screened by the study team to identify those who were discharged with a close fistula (Fig. 1). After locating them through their medical records, the study team (that includes nurses called “Fistula Counsellors” who are involved in the management of women at the fistula repair sites) will contact women by home visit in their community to obtain informed consent.

Once the informed consent is obtained, the woman will be interviewed for 30 − 60 min by the study team and examined in an isolated place for inclusion in the study. Later, her medical records will be used at the fistula repair site where she got the surgery to collect her sociodemographic and clinical characteristics at the time of surgery. For all women recruited in the study, most retrospectively, new fistula or recurrence of the repaired fistula, pregnancies and their outcomes (miscarriage, stillbirth, live birth, early new-born death, maternal death, and type of maternal complication) will be documented. Health Centres and Health posts around which the study participants live will be used by the study team to perform the dye test in women who report “Continuous and uncontrolled leaking” since discharge or at the follow up visit.

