**Fig. 2 Fig2:**
[figure not shown]
Study timeline

A home visit will then be conducted within the community to seek informed consent with the repaired women. After obtaining the consent, women will be interviewed. Women who report “Continuous and uncontrolled leaking” since the last follow-up visit will be scheduled for a pelvic exam and a dye test at the nearest health centre or health post. If the case is confirmed as fistula (by a dye test of clinical exam), the woman will be counselled and referred to the nearest fistula repair centre. By this approach, we think that any misclassification of outcome (recurrence of fistula) will be minimal, since women with any continuous and uncontrolled leakage of urine following repair are likely to report it, and any reported incontinence will be evaluated by a dye test.

If a woman reports pregnancy, she will be asked to show her antenatal care (ANC) & delivery card on which pregnancy test result is routinely reported. If possible, a pregnancy test will be performed. Otherwise, investigators will rely on woman self-reporting.

Sociodemographic and clinical characteristics of women will be collected from individual medical records at each participating fistula repair site.

All investigators will receive appropriate training at the Maferinyah National Research and Training Centre before they go in the field.

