### Data collection

#### Recruitment and follow-up visit

The enrolment and follow up data are collected using structured and pre tested standardised questionnaires. Both questionnaires will include participants’ current fistula status (fistula close and continent/closed but not continent), post-operative social and reproductive life (marital status, occupation, sexuality, use of modern contraceptive methods, pregnancy, childbirth), and any fistula related complication. Participants’ current full address is also collected to facilitate communication, referral and follow-up visits.

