#### Sociodemographic and clinical characteristics

After obtaining the informed consent during the recruitment visit, a standardised questionnaire called Baseline form is used to collect the demographic and clinical characteristics of women from hospital records in the hospitals where they were discharged from. This questionnaire includes age at presentation at hospital, marital status, age at marriage, occupation, level of education, residence (rural/urban), number of pregnancies, parity, number of previous repairs, and duration of fistula. Clinical characteristics include mode of delivery related to development of the fistula, neonatal outcome at causal delivery, type of fistula (VVF, RVF or both), status of the bladder neck, nature of the fistula according to the surgeon (simple versus complex), duration of catheterization after repair, status of the operating surgeon (expatriate, local trainer, local trainee), postoperative complications, context of repair (routine repair or pooled repair) and the status of the fistula at discharge (close and continent/Close but not continent).

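### The only stated follow-up screen for fistula recurrence asks about urine, so a recurrent or new rectovaginal fistula has no defined detection route; the look-back wording also differs between sections

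*Protocol article*

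**What the plan says.** All references are to the protocol article.

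- **Outcome definition (Methods, Study design).** "recurrence of fistula includes the breakdown of a repaired fistula or the occurrence of a new fistula in study participants". There is no limit to urinary fistula. The endpoint list at the end of the Background closes with "maternal, perinatal and child death at any time from hospital discharge", so events count from discharge onward.
- **Case mix.** The Background describes obstetric fistula as an opening that may involve the bladder, the rectum or both. The baseline form (Sociodemographic and clinical characteristics) records "type of fistula (VVF, RVF or both"). Participants' recruitment and follow-up admits "only women with a unique obstetric fistula that was closed at discharge, as measured by a dye test" and does not name rectovaginal fistula as an exclusion.
- **Screen at follow-up (Study design).** "women will first be asked about current medical status using the question" that follows, namely "does the woman have continuous and uncontrolled leakage of urine". The pelvic exam with dye test is scheduled if the answer is yes.
- **Other wording of the trigger.** Participants' recruitment and follow-up sends women to the dye test if they report leaking at any point after discharge or at the visit. Study procedures sends those who report leaking since the previous visit. Table 1 lists the dye test at enrolment and at follow-up with no condition.
- **Retrospective events.** Participants' recruitment and follow-up says that new or recurrent fistulas will be documented for all women, mostly by looking back.

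**The concern.** The screen is narrower than the outcome it serves. A woman whose repaired rectovaginal fistula breaks down, or whose bladder repair holds while a new rectal fistula forms, can truthfully answer no to a question about urine. Under the follow-up procedure as written she is not sent for examination.

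Two results are at stake. The primary incidence would be too low, and neither a larger sample nor the confidence interval would reveal it. The risk-factor analysis would also suffer: fistula characteristics are among the predictors of interest, and detection would depend on fistula type.

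A second gap concerns time. Women repaired before the study started enter retrospectively, so some recurrences may have been repaired again before anyone visits. An exam at the visit cannot show a fistula that is already closed. Pregnancy has a route for past evidence in Study design (medical records, or self-report backed by two witnesses); recurrence has no equivalent.

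**Working it through.** **Step 1: does the screen cover the outcome?** The sections side by side:

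| Element | Where | Covers rectovaginal fistula? |
|---|---|---|
| Definition of obstetric fistula | Background | Yes |
| Fistula type recorded at baseline | Sociodemographic and clinical characteristics | Yes |
| Inclusion criteria | Participants' recruitment and follow-up | Not excluded by name |
| Recurrence | Study design | Yes (any breakdown or new fistula) |
| Screening question at follow-up | Study design | No (urine only) |
| Exam and dye test | Study design | Only after a yes to the urine question |

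The first four rows admit the condition; the last two give it no defined route.

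**Step 2: which period does the question cover?** Study design asks about the present. Participants' recruitment and follow-up covers the time since discharge as well as the visit. Study procedures covers the time since the previous visit. These are three different triggers, and Table 1 states none.

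**Step 3: can a past recurrence be confirmed?** In Study design and Study procedures, confirmation is an examination arranged after the interview. A fistula closed again by then cannot be shown this way. Data analysis takes the date of recurrence as the event date but does not say how to obtain it in such a case. Classification and date are therefore undefined.

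**Step 4: size.** The plan gives no rectovaginal share and no re-repair rate, so there is no figure of its own to reproduce. To set a scale:

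- true risk p = 4.26 % (the six-month Ethiopian figure in the Background; its use as the true risk here is an assumption);
- planned sizes 280 and 364, and planned margin ±2 percentage points (Sample size calculation);
- m = share of recurrences missed (assumption, varied).

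Expected events are 280 × 0.0426 = 11.9 and 364 × 0.0426 = 15.5. Observed risk = p × (1 − m), and bias = p × m:

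| m | Observed risk | Bias (points) | Events lost, 280 / 364 |
|---|---|---|---|
| 5 % | 4.05 % | 0.21 | 0.6 / 0.8 |
| 10 % | 3.83 % | 0.43 | 1.2 / 1.6 |
| 20 % | 3.41 % | 0.85 | 2.4 / 3.1 |
| 30 % | 2.98 % | 1.28 | 3.6 / 4.7 |
| 50 % | 2.13 % | 2.13 | 6.0 / 7.8 |

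The bias reaches the planned ±2 points only when m = 0.02 / 0.0426 = 0.47, that is, when about 47 % of recurrences are missed.

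If recurrence is equally frequent in all types and no rectovaginal recurrence is found, m equals the share of women with rectovaginal fistula only. New rectovaginal fistulas in women first repaired for a bladder fistula would raise m above that share.

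**Step 5: effect on fistula type.** For rare events, observed rate ratio ≈ true rate ratio × (detection probability in rectovaginal cases / detection probability in bladder cases). If the second factor is below 1, rectovaginal fistula looks more protective, or less harmful, than it is.

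**The case against.** The strongest reply is that the plan has more routes to detection than the one question. Participants' recruitment and follow-up says that women are examined at inclusion, Table 1 lists the dye test without a condition, and two sections speak of leaking without naming urine. The questionnaires also collect fistula-related complications. This stands in part: some rectovaginal cases may be caught, so it would be too strong to say that these women are never examined. But the inclusion exam is unspecified, and none of these items is defined as a way to find a rectal fistula at follow-up. If the dye-test criterion at discharge was meant to confine the cohort to urinary fistula, the Background, the outcome definition and the baseline form say otherwise.

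A reader might also infer more than the text supports:

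- **That the screen asks only about current leakage and counts re-repaired recurrences as no event.** Two sections look back in time, recurrences are to be documented retrospectively, and Data analysis censors only women without recurrence. Nowhere does the text say that such women are event-free. What remains is inconsistent wording and no rule for confirming or dating these cases.
- **That the questionnaire cannot record an open fistula**, because the listed codes are "current fistula status (fistula close and continent/closed but not continent"). This is a parenthetical summary, and the questionnaire itself is not shown.
- **That "any reported incontinence will be evaluated by a dye test" contradicts the narrower trigger.** The phrase ends a sentence about continuous, uncontrolled urine leakage and can be read as meaning just that.
- **That incidence would fall to about 3.0 %.** This needs 30 % of recurrences to be missed, for which the documents give no basis.

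A condensed article may leave verification rules to the full protocol. That excuses missing detail, but not three different look-back periods or a screen narrower than the stated outcome.

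**Conclusion.** The concern holds in a limited form. Rectovaginal fistula belongs to the case mix and to the primary outcome as written, but the only stated follow-up screen addresses urine and controls access to the exam. Incidence is probably biased downward, and fistula type is distorted as a risk factor. The amount cannot be determined: with 5–10 % of recurrences missed, the understatement is 0.2–0.4 percentage points, or about 0.6–1.6 of the 12–16 expected events. That is small against ±2 points, but it runs in one direction and bears directly on one predictor.

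Separately, the sections disagree on the period the question covers, and a recurrence repaired again before the visit has no defined classification or date. In a largely retrospective cohort this needs a rule.

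The direction rests on the follow-up procedure being applied as written, and the size rests on the assumptions above. The point should be fixed and does not invalidate the design; confidence is moderate.

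**What to change.** 1. Add one screening item on leakage of stool or gas through the vagina, with a yes leading to the pelvic exam already planned. Alternatively, restrict the cohort and primary outcome explicitly to urinary fistula and align the baseline form with that.
2. Use one look-back wording in Study design, Participants' recruitment and follow-up, Study procedures and Table 1: since discharge at enrolment, since the last visit thereafter, with the date of onset. State in Table 1 whether the dye test is conditional.
3. Count as an event a repeat fistula repair after the index discharge if it is documented in study-site records, or self-reported with corroboration as Study design already allows for pregnancy. Site records alone are not enough: Specific setting mentions four repair sites in the country, of which three take part. State which date counts as the event date.

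The cost is a few questionnaire items and some linkage of repeat admissions in records that are already being screened. No new procedure is needed. Restricting to urinary fistula is cheaper still, but it narrows the question the study answers.
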